**Methods:**

The Tamil Nadu Pregnancy and Heart Disease Registry (TNPHDR) is a prospective, multicentric and multidisciplinary registry of PWWHD from 29 participating sites including both public and private sectors, across the state of Tamil Nadu in India. The TNPHDR is aimed to provide data on incidence of maternal and fetal outcomes, adverse outcome predictors, applicability of the modified World Health Organization (mWHO) classification of maternal cardiovascular risk and the International risk scoring systems (ZAHARA and CARPREG I & II) in Indian population and identify possible gaps in the existing management of PWWHD. Pregnancy and heart teams will be formed in all participating sites. Baseline demographic, clinical, laboratory and imaging parameters, data on counselling received, antenatal triage and management, peripartum management and postpartum care will be collected from 2500 eligible participants as part of the TNPHDR. Participants will be followed up at one, three and six-months after delivery/termination of pregnancy to document study outcomes. Predictors of maternal and foetal outcome will be identified.

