### Enrollment, inclusion, and exclusion criteria

The TNPHDR is a prospective observational registry enrolling all antenatal women seeking outpatient or inpatient care in any of the participating sites with known or newly diagnosed structural heart disease, cardiac rhythm disorders or aortopathy/vascular diseases from 15^th^ of January 2020 to 31^st^ March 2021 or till at least 2500 eligible participants are enrolled. Antenatal patients will be enrolled at any trimester when they first enter the institution. Women with eligible heart disease seen after delivery will be included in the first six weeks postpartum. Inclusion for women with peripartum cardiomyopathy will be allowed up to six months postpartum. Collected data will be protected for privacy with all standard precautions. For example, each enrolled participant will be assigned a unique autogenerated TNPHDR identification number by which they will be identified subsequently. The unique number will remain the same despite inter-institutional transfer. Patients with pregnancy related complications like gestational hypertension, anemia, eclampsia, and gestational diabetes without structural heart disease will be excluded from the TNPHDR. Patients with trivial / mild regurgitation of the cardiac valves will be excluded, unless associated with other eligible heart diseases.

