## Outcome measures

Primary outcome will be a composite of maternal cardiac events. Cardiac death, resuscitated cardiac arrest, cardiac hospitalization, new or worsening heart failure requiring treatment escalation or hospitalization, new episode of arrhythmia requiring treatment, thromboembolic event, hemorrhagic complications, aortic dissection, endocarditis, acute coronary syndrome, or cardiac intervention during pregnancy and up to 1 week post-delivery will be included as maternal cardiac events. Individual components of composite primary outcome and all-cause mortality will be the secondary outcomes.

We will include both obstetric and fetal outcomes as additional secondary outcomes. Obstetric outcome measures will include gestational diabetes mellitus, gestational hypertension (at least two blood pressure readings above 140/90 measured more than 6 h apart, after 20 weeks of gestation), pre- eclampsia (gestational hypertension with > 0.3 g proteinuria in the 24 h urine sample), eclampsia (pre-eclampsia with seizures) / HELLP syndrome (haemolysis, elevated liver enzymes, low platelet count), preterm labour (spontaneous onset of labour < 37 weeks of gestation), premature rupture of membranes (membrane rupture before onset of uterine contractions) and mode of delivery. Fetal loss (abortions defined as fetal death < 20 weeks, intra-uterine death defined as fetal death > 20 weeks and still births) will be the main fetal outcome considered in the study. We will also include a composite of fetal loss, premature birth before 37 weeks of gestation, intra-uterine growth retardation or small-for-gestational-age (birth weight < 10th percentile for gestational age or less than 2.5 kg) and congenital heart disease or anomalies in the newborn as additional secondary fetal outcome.

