### Data management and analysis

Data uploaded in the TNPHDR server will be verified for accuracy and completeness by the nodal coordinating centre team. Regular assessment will be done to check the appropriateness and completeness of the uploaded data. As required by the International Conference on Harmonisation Good Clinical Practice guidelines (ICH-GCP), the investigator will allow direct access to all registry related medical records to allow the verification of data gathered in the eCRFs and for the review of the data collection process*.* The nodal center staff will conduct periodic site visits to all participating centers to verify the data by random cross-check of the source documents (10% of all data fields), as part of quality assurance. We will use appropriate summary statistics to present the descriptive data. Multivariate regression models will be employed to study predictors of maternal and fetal outcomes.

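### Pooled fetal loss includes death before 20 weeks, which women enrolled later in an ongoing pregnancy cannot have, so its incidence over all participants depends on when they enter

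*Protocol article*

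**What the plan says.** Under Outcome measures, the article defines one pooled event, "Fetal loss (abortions defined as fetal death < 20 weeks, intra-uterine death defined as fetal death > 20 weeks and still births", and states that it "will be the main fetal outcome considered in the study". The same event is a component of the secondary fetal composite, next to birth before 37 weeks. Preterm labour is listed among the obstetric outcomes. All of these are secondary; the primary outcome is a composite of maternal cardiac events.

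Entry is open in time. Under Enrollment, inclusion, and exclusion criteria: "Antenatal patients will be enrolled at any trimester when they first enter the institution". Also: "Women with eligible heart disease seen after delivery will be included in the first six weeks postpartum". For one diagnosis the window is longer: "Inclusion for women with peripartum cardiomyopathy will be allowed up to six months postpartum".

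The Abstract says the registry is "aimed to provide data on incidence of maternal and fetal outcomes". Methods/Design adds the identification of predictors, a risk score for low- and middle-income settings and a management guideline. On analysis, Data management and analysis says "Multivariate regression models will be employed to study predictors of maternal and fetal outcomes". The article does not relate any fetal outcome to gestation at entry.

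**The concern.** A woman enrolled with an ongoing pregnancy after 20 weeks has already passed the period in which the early component could occur. If she is counted in the denominator of the pooled outcome, she contributes no early risk. This is left truncation, and it arises from two rules that the article itself fixes: the outcome definition and the entry rule.

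Two things are at stake. First, the reported incidence would partly measure when women reach the hospitals. Two registries with identical fetal risk but different booking patterns would report different figures. Second, a variable linked to early or late entry could pick up an association with fetal loss that reflects only the period observed. Known versus newly diagnosed disease might be such a variable, and so might the late-assessment item of CARPREG II, if it were used in a fetal model. The results are meant to feed a risk score and a guideline.

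The same mechanism affects preterm labour and birth before 37 weeks in women first enrolled, still pregnant, at or after 37 weeks.

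**Working it through.** The article states no fetal-loss rate, no distribution of gestation at entry and no derivation of the 2500, so there is no figure of the plan to reproduce. What follows is left-truncation arithmetic on assumed inputs.

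**Inputs**
- From the article: the outcome split at 20 weeks, the entry rule, N = 2500.
- Assumed: risk of loss before 20 weeks e = 3% to 10%; risk after 20 weeks l = 2% to 4%; share entering before 20 weeks s = 20% to 80%.
- Assumed: the early risk still ahead at entry, e', is either e (the whole early period is observed) or e/2 (half has passed).
- Every later entrant is given the whole of l. This flatters the crude figure, because part of that risk has also passed for a woman entering late.

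**Formulas**
- Full risk per pregnancy = e + (1 − e)l
- Risk in early entrants = e' + (1 − e')l
- Crude registry risk = s[e' + (1 − e')l] + (1 − s)l
- Late-versus-early-entry odds ratio (OR) = [l/(1 − l)] ÷ [odds of loss in early entrants], with no true effect of entry time

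**Worked case: e = 5%, l = 4%, s = 40%**
- Full risk = 0.05 + 0.95 × 0.04 = 8.8%.
- With e' = e: crude = 0.4 × 0.088 + 0.6 × 0.04 = 5.9%. The shortfall is 2500 × (0.0880 − 0.0592) = 72 losses.
- With e' = e/2: risk in early entrants = 0.025 + 0.975 × 0.04 = 6.4%; crude = 0.4 × 0.064 + 0.6 × 0.04 = 5.0%. The shortfall is 96 losses.
- OR = 0.43 or 0.61. The chance that it reaches two-sided p < 0.05 with 2500 women is about 1.00 or 0.76.

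**Range** (first value e' = e, second e' = e/2)

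| e, l, s | Full risk | Crude risk | Crude/full | Late vs early OR |
|---|---|---|---|---|
| 3%, 4%, 80% | 6.9% | 6.3% / 5.2% | 0.92 / 0.75 | 0.56 / 0.72 |
| 5%, 4%, 20% | 8.8% | 5.0% / 4.5% | 0.56 / 0.51 | 0.43 / 0.61 |
| 5%, 4%, 80% | 8.8% | 7.8% / 5.9% | 0.89 / 0.67 | 0.43 / 0.61 |
| 10%, 2%, 20% | 11.8% | 4.0% / 3.0% | 0.34 / 0.25 | 0.15 / 0.28 |

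Over the whole grid, the crude risk is 25% to 92% of the full risk, the OR is 0.15 to 0.72, and the chance of p < 0.05 is 24% to 100%.

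**Could postpartum entry cancel it?** Take e = 5%, l = 4%, s = 40%, e' = e, and 10% entering postpartum. The fetal-loss proportion they would need is (0.088 − 0.4 × 0.088 − 0.5 × 0.04)/0.10 = 33%. With 5% entering postpartum it is 62%; with 20% it is 18%.

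**Effect on another predictor.** Take two groups of 1,250 with identical risks, of whom 60% and 20% enter before 20 weeks.
- 8% early and 2% later: 0.6 × 0.08 + (1 − 0.048) × 0.02 = 6.7%, against 0.2 × 0.08 + (1 − 0.016) × 0.02 = 3.6%. OR 0.51 (95% CI 0.35 to 0.75).
- 4% early, 2% later: OR 0.63 (0.41 to 0.97).
- 4% early, 3% later: OR 0.70 (0.48 to 1.02).
- 2% early, 2% later: OR 0.75 (0.46 to 1.21).

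Now stratify the first case by entry before or after 20 weeks. Early entrants have 0.08 + 0.92 × 0.02 = 9.8% in both groups and late entrants 2% in both, so the adjusted OR is 1. Adjustment removes the artefact in this example. The pooled incidence is unchanged.

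**The case against.** The best reply is that an article condenses the full protocol. Denominators, risk sets, time scale and covariates normally sit in the full protocol or the analysis plan, and neither is shown. The article does not commit to a logistic model or to one common denominator. A delayed-entry model is compatible with what it says, and the outcome definition already names its parts on either side of 20 weeks, so separate reporting is open. All of that stands, and the point is therefore conditional on a pooled figure over all participants or a model that ignores entry time. It is not answered entirely, because the pooled main fetal outcome and the open entry rule are both set in this article, and incidence is a stated aim.

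A reader might infer more than the documents support:
- **That a false predictor is certain, or that late presentation will look protective.** The covariates are not listed, the article does not tie the CARPREG II item to fetal outcomes, and late presenters may have a true excess of later loss.
- **That adjustment is no help.** The stratified example shows otherwise for predictors.
- **That women cannot enter after an abortion.** The postpartum rule speaks of delivery, but antenatal inpatients are enrolled and follow-up runs from delivery or termination. The wording is loose; it is not a demonstrated exclusion.
- **That incidence must be understated.** Enough postpartum entry after a loss could offset it.

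**Conclusion.** The point holds in a limited form. As defined, the pooled fetal-loss proportion over all participants depends on gestation at entry. It understates loss per pregnancy from early gestation unless postpartum entrants carry a high fetal-loss proportion, about 33% if they are 10% of the registry in the worked case. Predictors correlated with entry time can be distorted if the model does not deal with entry time.

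The size cannot be taken from the article. Without offsetting postpartum entry, the direction was the same in every combination tried, but the extent and the statistical significance both depend on assumed loss risks and entry shares. Severity is minor to moderate: fetal loss is a secondary outcome, but it is the main fetal one.

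**What to change.** State the population at risk for each fetal outcome:
1. Report loss before 20 weeks only among women enrolled with an ongoing pregnancy before 20 weeks.
2. Report fetal death from 20 weeks and stillbirth among pregnancies ongoing at 20 weeks, or at enrolment if later. The present definitions leave death at exactly 20 weeks in neither group; this wording places it.
3. Fit the fetal predictor models with gestational age as the time scale and delayed entry at gestational age of enrolment. This also handles women who enter part-way through a risk period, for example at 15 or 36 weeks.
4. Use the same approach for preterm labour and birth before 37 weeks, excluding women enrolled at or after 37 weeks.
5. Report women enrolled after delivery or loss separately, because their fetal outcome is already known at entry.

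Enrolment and care do not change. The cost is some rewording, a little more analysis, and a wider interval for early loss because fewer women inform it. Gestational age at enrolment has to be available for every woman; the late-assessment item of CARPREG II already calls for information on timing.

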### Antenatal triage of cardiac patients

The antenatal patients with cardiac disease will be initially triaged as high-risk cardiac illness and low-risk cardiac illness during their registration based on the mWHO classification of maternal cardiovascular risk (Table 1). Patients belonging to mWHO I and II will be classified as low-risk, and patients belonging to mWHO II-III, III and IV as high-risk groups. More frequent follow up as per existing guidelines [23] will be recommended for high-risk patients including early hospitalization for safe delivery and child birth as appropriate. However, the frequency and components of follow up will be decided as per the discretion of the participating site investigators or according to the institutional protocol of each participating sites.

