### Post-partum care and follow up

All patients enrolled in the TNPHDR will be actively followed up for a period of 6 months from the date of delivery/termination of pregnancy. During this time data will be collected at one month, three-month and six-month time points either during the clinical visits or by telephonic calls. At least one clinical follow up including an echocardiographic assessment is mandatory during follow up (Fig. 2).

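### Neither fetal outcome counts death after live birth, so a newborn death is a non-event for the main fetal outcome and at best a preterm birth, low weight or anomaly in the composite

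*Protocol article*

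**What the plan says.** All outcome definitions stand in the Outcome measures section of the protocol article.

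- **Main fetal outcome:** "Fetal loss (abortions defined as fetal death < 20 weeks, intra-uterine death defined as fetal death > 20 weeks and still births", closing with the statement that this "will be the main fetal outcome considered in the study".
- **Additional fetal outcome:** "a composite of fetal loss, premature birth before 37 weeks of gestation", then growth restriction or small size ("birth weight < 10th percentile for gestational age or less than 2.5 kg"), then "congenital heart disease or anomalies in the newborn as additional secondary fetal outcome". The list ends there.
- **Mortality:** "Individual components of composite primary outcome and all-cause mortality will be the secondary outcomes". This sentence closes the paragraph on maternal cardiac events, before fetal outcomes are introduced.

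Other relevant sections:

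- Post-partum care and follow up: after delivery or termination, "data will be collected at one month, three-month and six-month time points".
- Antenatal triage of cardiac patients: more frequent follow-up is recommended for women in mWHO II-III, III and IV, "including early hospitalization for safe delivery and child birth as appropriate". The frequency and content of follow-up are left to the site investigator or institutional protocol.
- Data management and analysis: regression models are planned for predictors of maternal and fetal outcomes, without naming which fetal outcome is modelled.
- Study settings: site teams include pediatrics/neonatology.

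**The concern.** The fetal outcomes stop at an awkward place. Fetal loss ends at birth. The composite goes past birth to count the infant's weight and any anomaly, but it leaves out the most serious newborn event. This is not a detail waiting for a fuller document, because the article spells out both component lists with thresholds.

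The registry aims to measure fetal outcomes, to find their predictors, and to use the results for a risk score and a management guideline. If the definitions are followed as written, the analysis of the main fetal outcome puts an infant who dies on day 2 in the same category as a healthy survivor. In the composite, the death of a 2.4 kg infant carries the same value as the survival of one. The reported fetal results would then understate the deaths that followed these pregnancies, and no planned fetal outcome would show by how much.

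**Working it through.** **Step 1. Apply the definitions.** The table takes each kind of pregnancy result through the two fetal outcomes as written.

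| Result | Fetal loss | Composite |
|---|---|---|
| Abortion, intra-uterine death or stillbirth | event | event |
| Live birth before 37 weeks, infant dies | no event | event, as prematurity |
| Live birth at term, under 2.5 kg or below the 10th percentile, infant dies | no event | event, as low weight |
| Live birth at term, normal weight, anomaly, infant dies | no event | event, as anomaly |
| Live birth at term, normal weight, no anomaly, infant dies | no event | no event |

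No row scores a newborn death as a death. In rows 2 to 4 a surviving infant would score the same. The last row is counted in no fetal outcome. All-cause mortality does not fill the gap unless it is read as including the infant, which its place in the text does not suggest.

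**Step 2. How incomplete could fetal loss be?** The article gives no fetal or neonatal event rate, so there is no figure of its own to reproduce. Inputs:

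- N = 2461 enrolled (Study Status section, as of 5 November 2021).
- f = fetal loss, assumed 5% to 10%.
- n = neonatal death among live births, assumed 1% to 3%.
- Every pregnancy without fetal loss is taken as one live birth (assumed).

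Formulas: fetal losses = f × N; live births = N − fetal losses; neonatal deaths = n × live births; share missed = neonatal deaths / (fetal losses + neonatal deaths).

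| f | Fetal losses | Live births | n | Neonatal deaths | Share missed |
|---|---|---|---|---|---|
| 5% | 123 | 2338 | 1% | 23 | 23/146 = 16% |
| 5% | 123 | 2338 | 3% | 70 | 70/193 = 36% |
| 10% | 246 | 2215 | 1% | 22 | 22/268 = 8% |
| 10% | 246 | 2215 | 3% | 66 | 66/312 = 21% |

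Apart from rounding, the share equals n(1 − f) / [f + n(1 − f)]. It does not depend on N, so using the target of 2500 instead of 2461 changes nothing.

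**Step 3. What this does and does not show.** If fetal loss misses the same fraction m of deaths in every risk group, each group's risk is multiplied by (1 − m) and the risk ratios are unchanged. Distortion needs m to differ between groups.

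A purely conditional illustration takes two groups of 1250 with the same true risk p of fetal or newborn death. In one group a share s of would-be fetal losses occurs after live birth instead. The fetal-loss odds ratio is [p(1 − s) / (1 − p(1 − s))] / [p / (1 − p)]. For p from 4% to 12%:

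| s | Odds ratio for fetal loss |
|---|---|
| 10% | 0.89 to 0.90 |
| 25% | 0.73 to 0.74 |
| 50% | 0.47 to 0.49 |

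Counting both kinds of death gives 1.00 by construction. The illustration shows what a differential shift would do. It is no evidence that one occurs.

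**The case against.** A reader might infer that early delivery of high-risk women turns counted stillbirths into uncounted newborn deaths, and so biases the predictor models toward no effect. The documents do not support that reading.

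- The triage section recommends early hospitalization and leaves follow-up to the sites. It does not say that high-risk women are delivered at an earlier gestation.
- A birth before 37 weeks is already an event in the composite, as is a weight below 2.5 kg. The infant counted in no fetal outcome is a term infant, so delivery before 37 weeks cannot produce that case.
- The analysis section speaks of fetal outcomes in the plural. It does not say that fetal loss alone will be modelled.
- The direction of any bias is open. It depends on true differences between groups and on how the timing of death shifts, and the article reports neither.

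All four points stand, and the claim of biased predictors is not made here. Three more objections deserve an answer.

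- **The live-birth denominator is loose.** This is correct. Termination is advised for mWHO IV as applicable, and those pregnancies yield no live birth. Fewer live births would lower the missed share somewhat.
- **The case report form may already record neonatal death.** It may; it is a supplement and is not shown. Even so, no outcome in the article uses the item.
- **This is a choice of scope for a secondary outcome.** In part it is: fetal loss is accurately named, and the primary outcome is maternal. The composite, however, has already moved into the newborn period, so leaving out death there is a gap in its own terms.

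**Conclusion.** The point holds as a gap in the stated outcome definitions. It rests on the component lists alone and needs no assumption about care. Fetal loss misses every newborn death. The composite records such a death only through prematurity, low weight or anomaly, and misses it altogether in a term, normal-weight infant without anomaly.

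The figure of about 8% to 36% depends wholly on the assumed rates and on one live birth per pregnancy without fetal loss. It says how incomplete fetal loss would be as a count of deaths, not how biased any association is. If the timing of delivery differs by risk class, associations with fetal loss could also be distorted, but the article establishes neither that this happens nor its direction. The change is a low-cost improvement to a secondary outcome and does not affect the primary maternal analysis.

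**What to change.** 1. Define neonatal death as live birth followed by death by 28 days, and add it to the additional fetal composite.
2. Report fetal loss or neonatal death beside fetal loss, and repeat the fetal predictor models on it. Fetal loss stays as the main fetal outcome.
3. Take the infant's vital status from the one-month contact already scheduled. For women already past that point, use birth and neonatal records or the next scheduled contact. This group includes women enrolled late after delivery, since those with peripartum cardiomyopathy may enter up to six months postpartum.
4. State that all-cause mortality is maternal.

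The cost is one data item, possibly already on the case report form, one further outcome to report, and a repeat of the fetal models. The downside is some missing or retrospectively collected values for women enrolled early; their number should be reported. No existing outcome is removed and no clinical care changes.
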